#### *Nexfin*

Subject is fasting, no beverage with caffeine or sugar within 2 hours. The monitor is connected before 5 min rest in supine position without distraction. Non-invasive measurement of cardiovascular indices with a beat-to-beat pulse wave analyzer placed on the middle phalanx of one finger by Nexfin technology (ClearSight, Edwards Lifesciences). The ClearSight device comprises a pneumatic plethysmograph that provides advanced hemodynamic parameters and continuous noninvasive blood pressure (BP) from a finger cuff with a redesigned self-coiling mechanism that reconstructs the clinical standard brachial arterial waveform from the finger arterial pressure waveform; it has been validated towards invasive measurements in a number of clinical trials.

- Measurement of beat-to-beat blood pressure and pulse including pulse-contour analysis at rest and during physical tests.
- Registration of Heart rate, estimated Stroke volume, Cardiac index and Systemic vascular resistance index is recorded in the protocol.

#### *EndoPAT*

Subject is fasting, no beverage with caffeine or sugar within 2 hours. The monitor is connected before 10 min rest in supine position without distraction. Non-invasive determination of digital endothelial function is measured with a pulse amplitude tonometry (PAT) device placed on the tip of each index finger (Endo-PAT2000; Itamar Medical, Caesarea, Israel). The PAT device comprises a pneumatic plethysmograph that allows measurement of pulse volume changes.

Trial Code: HOT-LOCO  
Version No: v.4  
Date: 2022-01-03  
EudraCT No: 2021-000764-30

The PAT signal is recorded at baseline and following 5 min arterial occlusion using an inflatable blood pressure cuff placed on the forearm of one arm, while the contralateral arm serves as a control. The blood pressure cuff is inflated to 30 mmHg higher than the systolic pressure or a maximum of 200 mmHg for 5 min. The post-occlusive hyperemia stimulates endothelium-dependent vasodilatation causing an increase in digital pulse amplitude. The change from the baseline measurement is expressed as the reactive hyperemia index (RHI) which reflects vasodilator function of the digital microcirculation (Hamburg and Benjamin, 2009). Previous evaluation has demonstrated that reduced RHI reflects microvascular endothelial dysfunction, predicts cardiovascular events and reflects reduced NO bioavailability (Alexander et al., 2020).

### **Activity meter**

The commercially available OURA™ ring will be used. The OURA™ ring is worn like a finger ring and has a number of sensors that register heart rate, temperature and physical activity. With the OURA™ ring it is possible to monitor HRV, level of physical activity, changes in body temperature and sleeping pattern. Subjects will be asked to wear the OURA™ ring at a minimum 1 week before and after each visit. Data will be automatically registered in a smartphone application and then uploaded to a secure encrypted database.

### **Radiology**

Multiple different modalities of imaging are used in the clinical assessment including: Dual Energy Computed Tomography (DECT), Magnetic Resonance Imaging (MRI), Computed Tomography (CT) and normal chest X-ray (CXR). Review of records, document the time of radiology, reason for radiology and finding if it coincides with an interval of 12 weeks of visit 1, 3 4 and 5.

### **Socio-demography**

Demographic data such as gender, age, level of education, rate of employment/studies, level/rate of exercise, country of origin, body weight, height, and smoking habits/ nicotine use will be collected at Visit 1. Records and medical history will be reviewed for update/change in parameters at each visit.

### **Concomitant and post-trial treatment(s)**

Since Long COVID is a new syndrome, that may be chronic, without any definite cure, “best practice” for symptomatic medications and other treatments are likely to change over the course of trial. Subjects are also likely to have tried or may try other remedies.

Medications and treatments that are considered “best practice” may be given to the subjects at the discretion of their attending physician/physiotherapist/psychologist. Subjects will be discouraged to try new medications, treatments or remedies that are not evidence based during the course of the trial.

Trial Code: HOT-LOCO  
Version No: v.4  
Date: 2022-01-03  
EudraCT No: 2021-000764-30

Information regarding relevant regular concomitant medications, including vitamins, anti-oxidants, treatments and other remedies will be collected at Visit 1. Only relevant medications taken regularly, suspected to have caused an AE or used for treatment of an AE will be recorded. Changes in concomitant medications will be assessed (e.g. stop date or entry of a new treatment), throughout the trial by reviewing the patient's medical records and taking their medical history. Any changes will be recorded in the eCRF.

### **Blood samples**

Routine biochemistry for kidney function, liver function, cardiac insult, haematology and blood glucose will be registered from the hospitals electronic system if they are outside normal range.

Study-specific blood tests that will be collected are: Ferritin, D-Dimer, LDH, Troponin T and a pregnancy test for women of childbearing age.

Date and time of collection and results from routine and study specific blood tests are recorded in the eCRF.

Details regarding the handling of blood sampling for laboratory analysis are found in section 5.3.

### **HBO2 SOP and assessment**

A standard operation procedure (SOP) will be attached in the Trial Master File (TMF) but in general terms:

Subjects will be introduced to the hyperbaric unit; if required the subject may visit the unit before the first treatment. Treatment will be conducted in the multiplace (HAUX-STARMED-QUADRO 3500-2400) or monoplace chamber (SECHRIST 3300) depending on availability and number of subjects, at the discretion of the responsible physician. Subjects will be treated for 90 minutes; the treatment protocol is as follows - HBO2 240 kPa with 10 min compression time and 10 minutes decompression time, and two air breaks, while placebo entails - 134kPa air, with 5 min compression time, and 5 min decompression to 120 kPa, and two air breaks will be reported to the subjects. Pressure gauges that can be seen by subjects will be covered. The frequency of the treatments and timing will depend on available resources at the discretion of the responsible physician but should be 2–5 treatments per week for 2–4 weeks. No treatment must be given more than 6 weeks after randomization.

Date and time for treatment will be recorded. Any planned treatment that could not be delivered and reason for the cancellation will be recorded. The treatment will be recorded on a separate CRF accessible only to staff designated to the treatment but blinded for the investigators performing assessments. Treatment type will be recorded in the eCRF and medical records once the code is broken or at the end of trial.

### **AE and ADR**

Adverse events (AEs) and collection of AEs and Serious Adverse Events (SAEs) data.

|             |                |
|-------------|----------------|
| Trial Code: | HOT-LOCO       |
| Version No: | v.4            |
| Date:       | 2022-01-03     |
| EudraCT No: | 2021-000764-30 |

Collection of AEs will start directly after inclusion and will be recorded until visit 3. Only SAEs will be collected outside the treatment period (visit 2). Ongoing AEs and SAEs at the end of visit 3 will be followed up during long-term follow-up until the subjects last visit. Definitions, documentation and reporting of AEs are described in detail in the AE section below.

## 5.3 Biological sampling procedures

### 5.3.1 Handling, storage, and destruction of biological samples

Study-specific routine biochemistry will be analysed at the Karolinska University Hospital laboratory (KUL).

Study-specific biobanking includes collection of 4 extra tubes:

1x4ml EDTA plasma will be bio-banked for later analysis

2x8ml Citrate plasma (CPT-tubes) will be bio-banked for PBMC isolation and later analysis.

1x4ml heparin blood will be centrifuged and erythrocyte fraction will be incubated with CPH spin probe, bio-banked for later analysis of ROS in erythrocytes by EPR, plasma will be biobanked for later analysis.

CPT and EDTA tubes will be collected by a research nurse and transported immediately to the research laboratory Studieceter Karolinska where PBMCs are isolated, half are prepared with RNA-later® for later RNA extraction and gene expression analysis and half is cryopreserved for later functional analysis of the monocytes. The monocytes, citrate-, EDTA- and heparin plasma will be stored in a sub-biobank at Bioclinicum Karolinska University Hospital. The biological samples will be saved until all analyses are performed.

### 5.3.2 Total volume of blood per subject

The study-specific blood will be maximum 40 ml (24 ml for all and additionally 16ml for some subjects). A maximum total amount of 200 ml blood is collected from each subject at five visits over nine months. This volume should be related to a blood donor that donates 450ml at one occasion that can be repeated every four months for women.

### 5.3.3 Biobank

Plasma, erythrocytes and PBMCs collected in this trial are registered in a regional biobank with an agreement with *Stockholms Medicinska Biobank (IVO reg nr 914)* and handled according to the current biobank laws and regulations. The samples are coded/pseudonymized to protect the subject's identification. All samples and the identification/code list are stored securely and separately to prevent unauthorized access.

Trial Code: HOT-LOCO  
Version No: v.4  
Date: 2022-01-03  
EudraCT No: 2021-000764-30

## 5.3 End of Trial

The end of trial is defined as the last subject's final follow-up at visit 5 (week 52).

Premature termination of this clinical trial may occur because of a regulatory authority decision or at the discretion of the sponsor/the steering committee.

The sponsor/steering committee reserves the right to discontinue the trial at any time point in the following cases:

- Unexpected high proportion of AEs that are possibly or probably related to the trial drug.
- Trial protocol is difficult to cope with.
- Recruitment of eligible subjects is too low.

The end of the trial will be reported to the regulatory authority within 90 days, or 15 days if the trial is terminated prematurely. The Investigators will inform participants and ensure that the appropriate follow up is arranged for all involved.

## 6. Subject selection

### 6.1 Inclusion criteria:

To be included in the trial, subjects must meet the following criteria:

- 1) Aged 18–60 years
- 2) Healthy or mild systemic disease prior to COVID-19
- 3) Symptoms consistent with Long COVID for at least 12 weeks
- 4) Diagnosed with Long COVID, PACS, PCS (ICD-10 U09.9)
- 5) Working or studying prior to COVID-19
- 6) Documented informed consent according to ICH-GCP and national regulations

### 6.2 Exclusion criteria:

Subjects must not be included in the trial if any of the following criteria are met:

- 1) Known pregnancy or positive pregnancy test in women of childbearing age
- 2) ASA 3 or more from other cause than Long COVID
- 3) Score above 70 in RAND-36 domain Role Limitation Physical Health (RP) or Physical Functioning (PF)
- 4) Diabetes
- 5) Diagnosed with Hypertension prior to COVID-19
- 6) Contraindication for HBO2 treatment according to local guidelines
- 7) Participation or recent participation in a clinical trial with an investigational product
- 8) Mental inability, reluctance or language difficulties that result in difficulty understanding the meaning of trial participation

|             |                |
|-------------|----------------|
| Trial Code: | HOT-LOCO       |
| Version No: | v.4            |
| Date:       | 2022-01-03     |
| EudraCT No: | 2021-000764-30 |

## 6.3 Screening

Patients that have been assessed for Long COVID and that are likely to fulfil the inclusion criteria will be screened. Subjects will be informed about the trial by a study nurse during pre-screening and in detail about the trial by an investigator and after written informed consent, additional medical record review, HRQoL questionnaires, a HBOT specific questionnaire, physical examination (and pregnancy test if applicable) will be conducted. Subject eligibility (that subjects fulfill all inclusion criteria and do not meet any exclusion criteria) will be established before randomization to treatment.

## 6.4 Withdrawal Criteria

**Subject participation:** A subject will be considered to have completed the trial when he or she completes the assessment at 52 weeks (visit 5). Subjects should be encouraged to continue the trial but have the right to withdraw their consent or part of their consent regarding the trial participation e.g. to discontinue a study-specific blood test, but still participate in follow-up visits with questionnaires or not participate in further trial visits. The subject has no obligation to explain why he/she does not want to continue. The investigator also has the right to stop the subjects treatment in the event of AEs, protocol deviations, administrative reasons or any other reasons. It is understood by all concerned that an excessive rate of discontinues can render the trial uninterpretable. Therefore, unnecessary discontinuation should be avoided.

Irrespective of the reason for not continuing with the treatments and whenever possible, the patient should be examined. Relevant laboratory test samples should be obtained and all relevant assessments should be completed if applicable. All AEs should be followed up until they have returned to baseline status or stabilised.

A termination visit (End of trial) in the electronic case report form (eCRF) should be completed for every randomised subject whether the subject completed the trial or not. The reason for any early discontinuation should be indicated on this form.

Subjects may be discontinued from the trial at the discretion of the Investigator. Specific reasons for discontinuing a subject from further assessments are:

**AEs:** Clinical or laboratory events that in the judgment of the investigator, DSMB or the Sponsor and in the best interest of the subject constitute grounds for discontinuation. This includes serious and non-serious AEs regardless of relation to trial drug.

**Withdrawal of Consent:** If a subject withdraws consent for disclosure of future information at the discontinuation of the trial or after completion of the trial, no further evaluations should be performed and no additional data should be collected. The Sponsor may retain and continue to use data collected before subject withdrew his/her consent. The Withdrawal of Consent reason is only applicable if the subject denies any further contact with site and no further data collection.

|             |                |
|-------------|----------------|
| Trial Code: | HOT-LOCO       |
| Version No: | v.4            |
| Date:       | 2022-01-03     |
| EudraCT No: | 2021-000764-30 |

Lack of Efficacy/Treatment Failure: Subjects experiencing deterioration or no improvement of disease as judged by the investigator, may be discontinued from the trial at any time during the trial, offered alternative treatment and scored as treatment failures. Treatment failures includes significant disease worsening, requirement for surgical intervention and HBOT related SAE. Patients may be discontinued for sustained non-response at the discretion of investigator.

Protocol Violation: If the subject's findings, or conduct, fails to meet protocol entry criteria or fails to adhere to the protocol requirements that make it impossible to derive sound scientific or medical conclusions from the primary endpoint data generated on a subject, (e.g. diagnose is changed after randomization or wrong treatment is given according to randomization).

Lost to Follow-Up: The subject does not show up for further visits and study personnel cannot reach the patient.

Other: Termination of other reason

If the subject discontinues the trial, follow-up of this subject will be performed according to the clinic's routine but will be included in the Safety population if he/she have received at least one treatment.

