### 4.3 Primary endpoint:

Mean change from baseline to 13 weeks in RAND 36 domains role limitations due to physical health (RP) and physical functioning (PF).

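### Section 6.4 lets subjects be taken out of assessments for outcome-related reasons before week 13, and its treatment-failure score has no place in any endpoint or analysis

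*Protocol*

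**What the plan says.** Protocol section 6.4 opens its list of reasons with "Specific reasons for discontinuing a subject from further assessments are". The list includes adverse events, lack of efficacy or treatment failure, and protocol violation. Protocol violation covers cases where "diagnose is changed after randomization or wrong treatment is given according to randomization".

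Under lack of efficacy, subjects whom the investigator judges to have worsened or not improved "may be discontinued from the trial at any time during the trial, offered alternative treatment and scored as treatment failures". That item adds: "Treatment failures includes significant disease worsening, requirement for surgical intervention and HBOT related SAE". For anyone who leaves the trial, "follow-up of this subject will be performed according to the clinic's routine".

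The same section also pulls the other way: "Irrespective of the reason for not continuing with the treatments and whenever possible, the patient should be examined". It asks that relevant assessments be completed where applicable, says that subjects should be encouraged to stay, and warns that too many discontinuations could make the trial uninterpretable.

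Elsewhere in the protocol:
- Section 4.3: the primary endpoint is the mean change in RAND-36 RP and PF at 13 weeks. Section 9.2.4 analyses it by ANCOVA.
- Section 5.1: all treatment falls within 6 weeks of randomisation. The trial schedule has the visit 3 questionnaires sent digitally.
- Section 9.1.1: the full analysis set (FAS) keeps every randomised subject exposed at least once.
- Section 9.2.8: missing primary values are imputed, with observed cases as a sensitivity analysis. Secondary endpoints use observed data only.

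**The concern.** The list in section 6.4 ends assessments, not only treatment. A subject judged not to be improving can lose the week-13 questionnaire for a reason closely related to what that questionnaire measures. After the last session no trial treatment remains to be stopped, so a discontinuation between visits 2 and 3 ends only data collection.

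The failure score adds a second problem. The primary endpoint is a continuous change, and no endpoint in section 4 and no analysis in section 9 has a failure category. The protocol does not say what the score is for.

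At stake are a primary result that leans more on imputed values than it needs to, lost precision, and selective loss in every analysis that uses observed data. A questionnaire that was never sent cannot be recovered at the analysis stage.

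**Working it through.** **Step 1. The plan's own figure.** Section 9.2.1 gives a difference of 10, SD 15, a 5% level and 80% power. Section 9.2.2.2 makes tests two-sided. The two-sample t-test with standardised difference 10/15 = 0.667 needs n = 36.3, so 37 per group (power 80.8%). The stated 37 is reproduced. At 40 per group, power is 83.8%.

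**Step 2. Room for loss.** 80 − 2 × 37 = 6 subjects, or 6/80 = 7.5%. Section 7.5 allows no replacement. The document gives no dropout rate. If losses were equal in both arms and unrelated to outcome, 5%, 10%, 20% or 30% would give power of 81.8%, 79.7%, 74.7% or 68.8%.

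**Step 3. Where each rule leads for a subject discontinued for no improvement**

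| Question | Protocol answer |
|---|---|
| Is week 13 collected? | Not secured: further assessments end and follow-up is by clinic routine (6.4) |
| Is the subject in the FAS? | Yes, if exposed at least once (9.1.1) |
| Primary analysis | Value imputed (9.2.8) |
| Observed-case sensitivity analysis | Subject absent |
| Secondary endpoints | Later values absent, no imputation |
| Use of the failure score | None stated |

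**Step 4. Illustration of outcome-dependent loss.** From the protocol: difference 10, SD 15, 40 per arm. Assumed: mean change 5 on placebo and 15 on HBOT at both weeks 6 and 13, correlation 0.7 between the two changes, and a fraction f of subjects with week-6 change ≤ 0 removed.

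For an arm with mean μ, let a = −μ/15, p = Φ(a) and h = f·φ(a)/(1 − f·p). Among those remaining:
- fraction lost = f·p
- mean week-13 change = μ + 15 × 0.7 × h
- variance = 225 × [1 − 0.49 × (1 − v)], with v = 1 + a·h − h²

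Placebo: a = −0.333, p = 0.369, φ = 0.377. HBOT: a = −1, p = 0.159, φ = 0.242.

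With f = 1:
- Placebo: h = 0.377/0.631 = 0.598, mean = 5 + 10.5 × 0.598 = 11.28, SD 12.8.
- HBOT: h = 0.242/0.841 = 0.288, mean = 15 + 10.5 × 0.288 = 18.02, SD 13.6.
- Difference = 18.02 − 11.28 = 6.74.

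Power is from the noncentral t with the remaining n = 40 × (1 − f·p) and the remaining SDs, at the 5% level for one endpoint:

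| f | Lost, placebo / HBOT | n left | SD left | Observed-case difference | Power |
|---|---|---|---|---|---|
| 0 | 0 / 0 | 40 / 40 | 15 / 15 | 10 | 84% |
| 0.1 | 4% / 2% | 38.5 / 39.4 | 14.9 / 14.9 | 9.85 | 82% |
| 0.5 | 18% / 8% | 32.6 / 36.8 | 14.5 / 14.4 | 8.95 | 72% |
| 1 | 37% / 16% | 25.2 / 33.7 | 12.8 / 13.6 | 6.74 | 48% |

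**Step 5. No true difference.** If both arms have the same mean and the same f, the formulas give identical retained means, so the difference stays at 0.

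**The case against.** The strongest reply is that the protocol already limits the damage. The wording is permissive, staff are told to avoid unnecessary discontinuation, and relevant assessments are requested when treatment stops. Exposed subjects stay in the FAS with primary values imputed. RAND-36 is also collected at visit 2, so a week-6 score can inform the imputation, whose method may properly sit in the SAP. Assessors are blinded. All of this stands, and it confines the calculated bias to the observed-case analysis. It does not secure the week-13 value: the request for assessments is qualified, does not name week 13, and stands beside a list that ends assessments.

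Three stronger readings are tempting but not supported:
- *That the primary outcome is deleted.* The subject remains in the FAS and the value is imputed. It becomes informatively missing.
- *That adverse events and protocol violations are also scored as failures.* The phrase belongs only to the lack-of-efficacy item, which itself includes HBOT-related SAEs.
- *That scoring and imputation are two incompatible rules.* The score can be read as the discontinuation reason that section 6.4 requires on the termination form, which does not conflict with imputing a RAND-36 change. The text is unclear, but a contradiction is not shown.

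On size, holding the SD at 15 after selection would give power of 69% and 39% for f = 0.5 and 1. Those figures overstate the loss, because selection also narrows the spread of those who remain. Removing half or all non-improvers is an extreme assumption for a discretionary rule.

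**Conclusion.** The point holds in a limited form. Section 6.4 permits outcome-related loss of week-13 data that neither the length of treatment nor the mode of collection requires, and its failure score has no counterpart in any endpoint or analysis in the protocol.

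For the primary analysis, the consequence is more reliance on imputation and less precision. Its bias cannot be calculated, because it depends on an imputation method that is not shown. For the observed-case sensitivity analysis, the illustration gives a difference of 9.85 to 6.74 in place of 10, and power of 82% to 48% in place of 84%, as the removed share of non-improvers runs from 10% to 100%. The means, the correlation and the removal shares are assumptions, and the power figures ignore multiplicity across the two primary endpoints. Secondary endpoints on observed data are exposed to the same mechanism.

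A reader might infer a risk of a false-positive result. The documents do not support that: here the bias is toward the null, and it is absent when the arms do not differ and one rule applies to both. Direction and size would change only if removal differed between the arms in some other way. This is a cheap and worthwhile improvement, not a fault that invalidates the trial.

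**What to change.** Leave the clinical decisions in section 6.4 as they are, and reconcile its two parts so that stopping treatment is separate from stopping data collection:
- Every randomised subject who has not withdrawn consent continues the scheduled RAND-36 and EQ-5D questionnaires, week 13 in particular, whatever the reason for discontinuation.
- Those values enter the FAS analyses as observed.
- The failure-scoring phrase is deleted, or the protocol states that it is only a recorded reason for discontinuation with no role in any endpoint.

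The cost is a protocol wording change and a few extra digital questionnaires. Some week-13 values may then reflect alternative treatment. The protocol should say that they are used regardless, and the use of such treatment should be recorded so that its influence can be described.
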